## The LIAM Mc Trial

|                                                                      |                         |           |           |           |           |           |           |           |           |           |            |            |            |     |                         |
|----------------------------------------------------------------------|-------------------------|-----------|-----------|-----------|-----------|-----------|-----------|-----------|-----------|-----------|------------|------------|------------|-----|-------------------------|
| Muscle strength and mass assessment                      | X                       |           |           |           |           |           |           |           |           |           |            |            |            | X   |                         |
| Physical function and cardiovascular fitness assessment  | X                       |           |           |           |           |           |           |           |           |           |            |            |            | X   |                         |
| WCRF/AICR Questionnaire                                              | X                       |           |           |           |           |           |           |           |           |           |            |            |            | X   |                         |
| Timepoint                                                     | Screening
(-6 weeks) | Week
1 | Week
2 | Week
3 | Week
4 | Week
5 | Week
6 | Week
7 | Week
8 | Week
9 | Week
10 | Week
11 | Week
12 | EoT | Follow-up
(6 Months) |
| Baseline comprehensive nutrition assessment/ education   | X                       |           |           |           |           |           |           |           |           |           |            |            |            |     |                         |
| MST Score Assessment                                                 | X                       |           |           |           |           |           |           |           |           |           |            |            |            | X   |                         |
| 24-hour Dietary Recall                                               | X                       |           |           |           |           |           |           |           |           |           |            |            |            | X   |                         |
| Food Frequency Questionnaire                                         | X                       |           |           |           |           |           |           |           |           |           |            |            |            |     | X                       |
| Programme Induction                                                  |                         | X         |           |           |           |           |           |           |           |           |            |            |            |     |                         |
| Nursing Assessment                                                   |                         | X         |           | A         |           | A         |           | A         |           | A         |            | A          | X          | X   | X                       |
| EORTC- QLQ-C30 Questionnaire                                         | X                       |           |           |           |           |           |           |           |           |           |            |            |            | X   | X                       |
| ASAS-R Questionnaire                                                 | X                       |           |           |           |           |           |           |           |           |           |            |            |            | X   | X                       |
| EORTC Cancer Related Fatigue Score                                   | X                       |           |           |           |           |           |           |           |           |           |            |            |            | X   | X                       |

## The LIAM Mc Trial

|                                                                               |   |   |   |   |   |   |   |   |   |   |   |   |   |   |   |
|-------------------------------------------------------------------------------|---|---|---|---|---|---|---|---|---|---|---|---|---|---|---|
| Signposting to Other Services                                     | X | X | X | X | X | X | X | X | X | X | X | X | X | X | X |
| Social Work Education                                             |   |   |   | X |   |   |   |   |   |   |   |   |   |   |   |
| Nutritional Assessment/Education                                  |   |   | x |   | X |   | x |   | X |   | X |   |   |   |   |
| Occupational Therapy/physiotherapy                                |   |   |   |   |   | X |   |   |   |   |   |   |   |   |   |
| Nurse led education                                               |   |   |   |   |   |   |   | X |   |   |   |   |   |   |   |
| Pastoral care (spirituality & emotional reasoning)                            |   |   |   |   |   |   |   |   |   | X |   |   |   |   |   |
| Usability, Feasibility & Satisfaction Feedback questionnaires    |   |   |   |   |   |   |   |   |   |   |   |   |   | X |   |
| PPI workshop invitation and Invitation to Qualitative Interview  |   |   |   |   |   |   |   |   |   |   |   |   |   | X |   |
| Qualitative Interview (not all participants)                                  |   |   |   |   |   |   |   |   |   |   |   |   |   | X | X |

### Abbreviations:

X – Scheduled Activity

A – Available on request

EoT – End of Treatment (**Note:** EoT assessments to be carried out during week 12 of intervention programme or within 2 weeks of completing the programme).

### Footnotes:

 Body composition assessment to include Bioelectrical Impedance Analysis [BIA]/ultrasound assessment

## The LIAM Mc Trial

 Muscle strength and mass assessment to include 8 repetition maximum, thigh circumference

 Physical function and cardiovascular fitness assessment to include grip strength, 6-minute walk test [6MWT]

 Comprehensive nutrition assessment and education to include comprehensive diet history, anthropometric measurements, dietary analysis & dietary advice

 Services include: Psychosocial Coaching, ARC House, Pharmacist Medication Review, Nursing Review, Medical Review, Social Work Supports, Psycho-Oncology Supports, Other – as required. **Note:** Referral to these services will be an available option throughout the programme, with particular signposting and reminder sessions as highlighted in the schedule of activities.

 Social Work education session should include stress management and psychosocial support

 Nutritional assessment and education is aimed to revisit dietary analysis results and adjust tailored advice as appropriate

 Occupational Therapy/Physiotherapy should include fatigue management, pacing strategies and sleep hygiene.

 Nurse led education session on symptom management of side effects of treatment.

 Patient feedback questionnaires and thank you session.

 Invitation to quarterly PPI engagement meetings and PPI workshops to provide feedback for service improvement. Invitation to qualitative interviews serves to provide feedback and aid programme improvement.

## 6.0 Statistical Plan

---

### 6.1 Sample size justification

Parallel Sampling Groups will be used from Q3 of Year 1 on (after completion of the 6 participant Initial Phase). A new group of 6 participants will commence the programme every 6 weeks, in order to facilitate workload and resource management (see Figure 2, Section 3.2.1). This will mean two groups are at two different timepoints in the programme at any given date. 12 groups of 6 men each are planned in total, including the pilot phase group, with a total anticipated accrual of 72 participants over two years.

Given that the main objectives of this study are to evaluate the *feasibility* of introducing a men's malignancy survivorship programme, we have not calculated the sample size that would be required to reliably estimate the effect of the programme on patient outcomes. This follows from established best practices in pilot and feasibility studies [19] for which there is usually too much uncertainty in the various factors that are needed to make a sample size calculation robust (e.g. effect sizes of interest, outcome variability, etc.). Our sample size justification is instead based on trying to recruit the largest possible sample given existing financial and pragmatic constraints. This will allow us to maximize our ability to identify barriers to implementation, as well as the information that will be required to properly design any subsequent trials of the programme's efficacy (e.g. robust estimation of estimator variability, even for binary outcomes [20]). At the same time, the potential costs of over-recruitment are largely absent for this study. Most importantly, there are no excess risks to patients receiving the intervention, and all patients are guaranteed access to the current standard of care. Further, most of the financial costs of the study are fixed, regardless of the actual number of patients recruited into the study.

Given that the goal of a feasibility study is to identify problems that would impede the conduct of a larger, efficacy study, we have set the sample size at 60 based on advice from Viechtbauer et al. [21], which is aimed at being able to detect failures in study processes that would occur just 5% of the time (with 95% confidence). A sample size of 72 allows for sample attrition from men withdrawing, illness, or waning commitment as commented.

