|                  | 
 
Please see Section 4.1 and 4.2, Inclusion & Exclusion Criteria for full list and description.
 
                                                                                                                                                                                                                                                                                                                                                                                                                                                                                                                                                                                                                                                                                                                                                      |
| Intervention     | 
Men's Cancer Survivorship Programme:
 
A 12-week group-based interventional programme is proposed for men with advanced genitourinary cancers, encompassing intensive multidisciplinary input to provide men with personalised tools and coping mechanisms for life with cancer. The programme is based upon providing a supportive and safe enabling environment for the introduction of self-care interventions using a group-based format supported by individualised counselling according to the participant's identified needs. This will involve an allied health professional-led programme to include physiotherapist input twice per week, dietitian input two-weekly, specialist nursing input weekly, medical social worker input and psycho-oncology input weekly, with programme oversight by medical oncologists, in the Mardyke Arena, University College Cork (UCC).
 |

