## The LIAM Mc Trial

This initial phase, 12-week programme of the first 6 men will be completed and analysed, including follow up and analysis, prior to commencement of the Expansion Phase from Q3 of year 1 onwards, see 3.2.1, Gantt Chart.

In the Expansion Phase, and for the remainder of the study period, parallel sampling groups will be used (i.e. after completion of the 6 participant Initial Phase). A new group of 6 participants will commence the programme every 6 weeks, in order to facilitate workload and resource management, see Figure 2. This will mean two groups are at two different timepoints in the programme at any given date. In total, 12 groups of 6 men are planned, including the initial phase group, with a total anticipated accrual of 72 participants over the two-year study period.

Data collection will occur at three designated timepoints; Baseline/Screening, and End of Treatment visit (after completing the intervention) and at 6 months post intervention. Completion of a process evaluation as part of the feasibility testing and secondary outcome measurement will also occur after all participants have completed the 12-week intervention programme.

**Subject recruitment:** June 2023-June 2025.

**Subject follow up period:** September M 2023-l December 2025 (12-18 months recruitment until 72 patients recruited + 6 months follow up for last patient enrolled)

Final data analysis: February 2026-

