#### 4.4.3 Survivorship Programme Procedures

The survivorship programme is a 12-week group-based interventional programme for men with advanced cancer, encompassing intensive multidisciplinary input to provide men with personalised tools and coping mechanisms for life with cancer. The programme is based upon providing a supportive and safe enabling environment for the introduction of self-care interventions using a group-based format supported by individualised counselling according to the participant's identified needs. This will involve an allied health professional-led programme to include physiotherapist input twice per week, dietitian input every 2 weeks, specialist nursing input every 2 weeks, medical social worker input and psycho-oncology input, with programme oversight by medical oncologists, in the Mardyke Arena, UCC. An outline of the programme is provided in the 12-week intervention programme (Section 4.3.2) and Study Calendar (Section 5.0).

Research and relevant Clinical Staff will be trained in the protocol. Following successful completion of the Ethics Committee approved informed consent process, a unique study identifier will be applied to all subject's study data

and will be used exclusively as a unique identifier in study Case Report Forms. Subject's clinical notes will be reviewed, and an appointment arranged for the baseline visit.

The initial visit in the Mardyke Arena, UCC will assess and manage current symptomatology and needs per management pathways, refer to appropriate specialists, and ensure future access to the clinic where needed during the study period. Patients will receive education, exercise, diet and symptom management plan, depending on the outcome of the baseline assessments, or according to clinical judgement. The baseline physical and nutritional assessments will be undertaken at this visit. Diet education and personalised nutrition counselling will be performed throughout the study (For further information see Nutritional Intervention section 4.4.3.2).

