### The exercise intervention:

Participants will complete twice-weekly combined resistance and high/moderate intensity aerobic sessions.

It will be undertaken in small groups of up to 6 participants for approximately 60 minutes under the supervision of a physiotherapist, dietitian and candidate Advance Nurse Practitioner in an exercise clinical setting.

Exercises will target the major muscle groups

The exercises will be performed based on a modular approach to avoid loading the affected area and minimising the mechanical forces placed on the affected structures, based on the table below.

| Metastases site     | Resistance |       |       | Aerobic |     | Flexibility |
|---------------------|------------|-------|-------|---------|-----|-------------|
|                     | Upper      | Trunk | Lower | WB      | NWB | Static      |
| Pelvis              | ✓          | ✓     | ✓**   |         | ✓   | ✓           |
| Lumbar spine        | ✓          |       | ✓     |         | ✓   | ✓***        |
| Thoracic spine/ribs | ✓*         |       | ✓     | ✓       | ✓   | ✓***        |
| Proximal femur      | ✓          | ✓     | ✓**   |         | ✓   | ✓           |
| All regions         | ✓*         |       | ✓**   |         | ✓   | ✓***        |

✓, target exercise region; \*, exclusion of shoulder flexion/extension/abduction/adduction – inclusion of elbow flexion/extension; \*\*, exclusion of hip extension/flexion – inclusion of knee extension/flexion; \*\*\*, exclusion of spine/flexion/extension/rotation; NWB, nonweight bearing (e.g. cycling); WB, weight bearing (e.g. walking). Reproduced from [102].

[https://www.researchgate.net/profile/Nicolas-](https://www.researchgate.net/profile/Nicolas-Hart/publication/317013384/figure/tbl1/AS:670328686641169@1536830221355/Modular-multimodal-exercise-programme-for-patients-with-bone-metastases.png)

[Hart/publication/317013384/figure/tbl1/AS:670328686641169@1536830221355/Modular-multimodal-exercise-programme-for-patients-with-bone-metastases.png](https://www.researchgate.net/profile/Nicolas-Hart/publication/317013384/figure/tbl1/AS:670328686641169@1536830221355/Modular-multimodal-exercise-programme-for-patients-with-bone-metastases.png)

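### The 95% chance of detecting a 5% process failure holds for failures that strike men independently; for failures with one opportunity per group, 12 groups give 46%

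*Protocol*

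**What the plan says.** Section 6.1 (Sample size justification) says that no sample size was calculated for estimating effects on patient outcomes, and that the aim is the largest sample that money and practicality allow. It then sets 60 men by a published rule for pilot studies, "which is aimed at being able to detect failures in study processes that would occur just 5% of the time (with 95% confidence"). The step from 60 to 72 is explained as "A sample size of 72 allows for sample attrition from men withdrawing, illness, or waning commitment as commented".

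The same section fixes the delivery structure: "12 groups of 6 men each are planned in total, including the pilot phase group". Section 4.4.3 repeats it: "The survivorship programme is a 12-week group-based interventional programme for men with advanced cancer". The exercise component is shared too: "It will be undertaken in small groups of up to 6 participants for approximately 60 minutes under the supervision of a physiotherapist".

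The provisional schedule in Section 4.3.2 and the table in Section 5.0 place the social work, occupational therapy, nurse-led and pastoral care sessions once each in a 12-week cycle. Section 6.1 does not mention dependence between men in the same group, and it does not limit the 95% statement to failures that affect men one at a time.

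**The concern.** The pilot-study rule asks how many independent chances are needed to see at least one failure. Section 6.1 uses the man as the unit, yet some of the processes under test are delivered to six men at once. If such a process fails, it fails for the whole group, and the number of chances is the number of groups.

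This is the only quantitative performance claim made for the sample size. The primary objective is feasibility, and Section 2.1 plans to offer the programme to all patients as standard care if it proves feasible. A reader of the final report could take the absence of any group-level failure as ruling out a 5% rate, on the strength of Section 6.1. Twelve groups cannot support that.

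**Working it through.** **Inputs.** From Section 6.1: failure rate p = 0.05, target probability 0.95, 60 men required, 72 recruited, 12 groups of 6. From Section 4.3: two sessions a week for 12 weeks, so 24 sessions per group and 12 × 24 = 288 in all. The protocol gives no intra-group correlation (ρ), so every value of ρ below is an assumption.

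**1. The protocol's own figure.** n = ln(0.05) / ln(0.95) = 58.4, so 59 men are needed and 60 is adequate.
- 60 men: 1 − 0.95^60 = 0.954.
- 72 men: 1 − 0.95^72 = 0.975.

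Both expressions treat the men as independent.

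**2. One opportunity per group.** Reading 5% as the rate per group:
- 12 groups: 1 − 0.95^12 = 1 − 0.540 = 0.460.
- Lowest rate that 12 groups detect with 95% probability: 1 − 0.05^(1/12) = 0.221.
- Groups needed for 95% at a 5% rate: 59, by the formula in step 1.

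Retaining 72 men instead of 60 leaves these figures unchanged, because the number of groups stays at 12.

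**3. Partly clustered failures.** A beta-binomial model within groups has a = p(1 − ρ)/ρ and b = (1 − p)(1 − ρ)/ρ. For a group with m chances, P(no failure) is the product over i = 0 to m − 1 of (b + i)/(a + b + i). Detection is 1 − P(no failure)^12. For example, with ρ = 0.1 and m = 5, a = 0.45 and b = 8.55; P(no failure) = 0.8085 and detection = 0.922.

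| Assumed ρ | 12 groups of 5 (60 men) | 12 groups of 6 (72 men) |
|---|---|---|
| 0 | 95.4% | 97.5% |
| 0.05 | 93.9% | 96.2% |
| 0.1 | 92.2% | 94.7% |
| 0.3 | 84.4% | 87.2% |
| 0.5 | 75.2% | 77.5% |
| 1 | 46.0% | 46.0% |

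**4. Recurring sessions.** The same model with m = 24 sessions in each of 12 groups and 5% per session gives 99.9% at ρ = 0.1, 97.6% at 0.3 and 90% at 0.5. With independent sessions, detection is above 99.99%.

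**The case against.** The strongest reply is that 46% is an extreme case and that most of what this study watches is not of that kind. Much of this stands.

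- A reader might infer that a cancelled session, an absent professional or a venue problem on the day is detected with probability 46%. The documents do not support that. These are usually session events with 288 chances, and step 4 shows detection above 95% unless clustering is strong.
- Most feasibility outcomes in Section 6.2 are counted per patient: assessments completed, participation in all activities, need for medical review. The man is the natural unit there.
- A group missing its measurements together is not what the protocol describes. Baseline is taken within a 6-week screening window, and end-of-programme measures may be taken up to 14 days after completion.
- Section 4.4.7 keeps everyone who starts in the overall analysis. With all 72 men, mild clustering costs little: 96.2% at ρ = 0.05 and 94.7% at 0.1.
- No rule in the protocol turns an absence of failures into a declaration of feasibility. Section 3.3 makes that judgement multifactorial, and Section 4.4.4 already has implementation problems catalogued as they arise.

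None of this makes the unqualified sentence in Section 6.1 correct for processes delivered once to each group. The schedule contains several of these.

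**Conclusion.** The concern holds, within limits. The arithmetic behind 60 is right, and it would be wrong to conclude that the sample size is miscalculated or that 46% is the study's general detection probability. The fault is that Section 6.1 states the 95% property for study processes in general, while the design has it only where failures strike men independently.

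For a given process with one opportunity per group, a true 5% rate would be missed 54% of the time, and 95% detection begins at about 22%. These figures assume that 5% is read as a per-group rate, that all 12 groups run, and that groups are independent of one another. Between the two extremes the loss depends on a correlation the protocol does not give. Under the assumed values it runs from a few percentage points or less at 0.05 to about 10 points at 0.3, measured against the independent figure for the same number of men.

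**What to change.** Revise the last paragraph of Section 6.1 in three respects:

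1. Limit the 95% statement to participant-level failures that occur independently: 95.4% with 60 men, 97.5% with 72.
2. Add that, for failures with one opportunity per group, 12 groups give 46% detection at a 5% rate and reach 95% only at about 22% or more.
3. State that the implementation problems catalogued under Section 4.4.4 will be classified and reported by level, each with its own denominator: men enrolled, sessions scheduled (288 if all run, read with clustering by group in mind), and groups (12). State also that seeing no group-level failure does not exclude a 5% rate.

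The cost is one paragraph and one classification field in the implementation log. The stated figure becomes less favourable for one class of failure. Enrolment, group size and schedule do not change.
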